## Abstract

**Methods and Analysis::**

This ELEVATE trial is a prospective, single-center, single-arm, non-blind, non-randomized trial to evaluate the usefulness of a TP measurement device for dysphagia associated with the treatment of HNC. Eligible participants include patients with oropharyngeal or hypopharyngeal cancer (HPC) undergoing RT or chemoradiotherapy (CRT). The TP measurements are conducted before, during, and after RT. The primary endpoint is the change in the maximum TP values from before RT to 3 months after RT. Moreover, as secondary endpoints, the correlation between the maximum TP value and the findings of video-endoscopic and video-fluoroscopic examinations of swallowing will be analyzed at each evaluation point, as well as changes in the maximum TP value from before RT to during RT and at 0, 1, and 6 months after RT.

**Discussion::**

This trial aimed to investigate the usefulness of evaluation by measuring TP for dysphagia associated with HNC treatment. We expect that an easier evaluation for dysphagia will improve rehabilitation programs for dysphagia. Overall, we expect this trial to contribute to the improvement of patients’ quality of life (QOL).

## 1. Introduction

Earlier, surgery was the mainstay of treatment for head and neck cancer (HNC); however, treatment algorithms have changed to include postoperative or definitive chemoradiotherapy (CRT).^[1–3]^ These changes in treatment options have been developed to improve survival, including in recurrent or metastatic settings.

While the number of cancer survivors is increasing, they often suffer from functional disorders, and their quality of life (QOL) declines after treatment.^[4]^ Dysphagia is a significant issue that is relevant to the decline of their QOL, and previous research has demonstrated that it leads to a decline in activities of daily living.^[5]^ As Japan already has a hyper-aging society, preventing dysphagia is a critical issue.

The normal swallowing process is generally classified into oral, pharyngeal, and esophageal stages according to the location of the bolus.^[6]^ In the oral stage, the movement of the tongue, including tongue pressure (TP), plays a key role in transiting the bolus to the oropharynx.^[7–9]^ A lower maximum TP is associated with oral residue and can lead to swallowing dysfunction.^[10]^ Moreover, aging can be a risk factor for lower TP.^[10]^

Radiotherapy (RT) is an important treatment modality for HNC; however, it damages the tumor as well as healthy oral and pharyngo-laryngeal tissues. Dysphagia is developed in approximately half of the patients with HNC as acute and late adverse events (AEs) by RT.^[4,11]^ AEs developed due to RT, such as xerostomia, pain, mucositis, and decreased tongue volume, can induce swallowing dysfunction.^[12,13]^ Regardless, there is no unified view of the correlation between RT and the change in TP, and the incidence and extent of the change have not yet been sufficiently clarified.^[14–16]^ However, RT should decrease TP since it has been clearly shown to induce muscle damage.^[17]^

The usefulness of TP measurement has recently been demonstrated in evaluating swallowing function in patients with neurological diseases and sarcopenia.^[5,18]^ In stroke patients, lower TP, linked to lingual discoordination, can result in swallowing problems in the oral stage.^[19]^ Moreover, TP has been reported to be a good predictor of oral-stage dysphagia.^[20,21]^ The TP measurement device provides objective data that can be easily used to evaluate patients’ swallowing function.^[21,22]^ However, the usefulness of evaluating swallowing function using a TP measurement device has not been established in patients with HNC. Additionally, although videoendoscopic examination of swallowing (VE) and video-fluoroscopic examination of swallowing (VF) are performed as general evaluations for dysphagia, there is a lack of quantitative examinations that evaluate the swallowing function of patients with HNC.^[23,24]^

In this trial, we aim to investigate the usefulness of the TP measurement device as a quantitative evaluation method for dysphagia in HNC patients. Our findings will help improve rehabilitation programs for dysphagia and contribute to the improving the QOL of patients.

## 2. Methods

### 2.1. Study design

This clinical trial, currently ongoing at Nara Medical University Hospital, is a prospective, single-center, single-arm, non-blind, non-randomized clinical trial involving patients with oropharyngeal (OPC) or hypopharyngeal (HPC) cancer who undergo CRT or RT as the standard cancer treatment. Participants will undergo rehabilitation for dysphagia (RD) and several examinations, including TP measurement, VE, VF, cervical computed tomography, ultrasound examination, blood test, chest radiography, electrocardiogram, and respiratory function test. Moreover, AEs will be evaluated according to the Common Terminology Criteria for Adverse Events Version 5.0, as proposed by the National Cancer Institute.

### 2.2. Inclusion criteria

Patients with OPC or HPC who underwent CRT or RT as primary treatment, including those who underwent neoadjuvant chemotherapy before CRT or RT.Age range: 18 to 85 years (regardless of gender).Eastern Cooperative Oncology Group performance status of 0 or 1.Patients who have provided written informed consent to participate in this study by themselves or through their surrogates.

### 2.3. Exclusion criteria

Patients who cannot understand the investigators’ indications.Patients who cannot maintain the TP probe in an appropriate position using their front tooth.Patients who are unable to apply pressure on the TP probe.Patients with dysphagia caused by past treatment for HNC.Patients with severe dysphagia due to a history of central system disease.Patients who are deemed unsuitable as research subjects by the investigator.

### 2.4. Discontinuation criteria

Patients whose TP is difficult to measure due to other conditions (cancer progression and/or AEs) during or after treatment.Patients who decline study participation.Patients who avail the offer to withdraw consent.Patients who do not meet the eligibility criteria after registration.Patients who are unable to come to the hospital due to relocation or other reasons.The entire study is discontinued.The study has been discontinued for other reasons that the investigators deemed appropriate.

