#### 2.5.1. Method of TP measurement.

After the participants are fully informed, TP is measured 3 times at each evaluation point by a TP measurement device (JMS Tongue pressure measurement device. JMS Co., Ltd.), and the maximum TP values are recorded. After treatment, the change in TP value is analyzed. If TP measurement is impossible, it is recorded as “Impossible” accompanied by a description of the reason.

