### 2.6. Endpoints

#### 2.6.1. Primary endpoint.

The primary endpoint was the change in maximum TP value from baseline to 3 months after RT.

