#### 2.8.1. Primary endpoint.

The average and 95% CI of the changes in the maximum TP value from baseline 3 months after RT will be analyzed as the primary endpoint. Moreover, the ratio of patients with “Impossible” will be calculated.

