#### 2.8.2. Secondary endpoint.

The average and 95% CI of the changes in the maximum TP value from baseline during RT, as well as 0, 1, and 6 months after RT will be analyzed as secondary endpoints. The ratio of patients with “Impossible” will be calculated as well.The change in the Hyodo score between the baseline and each evaluation point will be analyzed. The averages and 95% CI for the changes will be calculated. Moreover, the scatterplot and Pearson correlation coefficient between the Hyodo score and maximum TP value will be calculated.Dysphagia was evaluated based on the findings of VF at each evaluation point and the ratio of dysphagia among all participants, and the 95% CI of that will be calculated. Moreover, for participants in the group with dysphagia, the average and the 95% CI of both the maximum TP values and Hyodo score will be calculated.

For all the above endpoints, subgroup analyses will be conducted by subject characteristics (e.g., background information) to explore factors that may be useful in determining future research and treatment strategies.

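### Tongue pressure that cannot be measured is both a ground for discontinuation and a result to be counted at each visit, so patients can be lost for outcome-related reasons before the 3-month primary endpoint

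*Protocol article*

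**What the plan says.** Section 2.4 of the protocol article gives, among the discontinuation criteria: "Patients whose TP is difficult to measure due to other conditions (cancer progression and/or AEs) during or after treatment". It does not ask that the difficulty persist, and it does not say whether visits continue after discontinuation.

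Section 2.5.1 handles the failed measurement differently: "If TP measurement is impossible, it is recorded as “Impossible” accompanied by a description of the reason". Section 2.8.1 then adds, beside the mean 3-month change and its 95% CI: "Moreover, the ratio of patients with “Impossible” will be calculated". Section 2.8.2 repeats this for the visits during RT and at 0, 1 and 6 months: "The ratio of patients with “Impossible” will be calculated as well".

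The endpoint at stake is in Section 2.6.1: "The primary endpoint was the change in maximum TP value from baseline to 3 months after RT". Under Section 2.8 the full analysis set leaves out only patients with no maximum TP data at all. No numeric value is assigned to 'Impossible'.

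**The concern.** The two sets of rules treat much the same event in opposite ways. Ratios of 'Impossible' at successive visits describe the cohort only if a patient unmeasurable at one visit is still followed at the next. Section 2.4 allows that patient to be taken out.

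Several TP measurements come before the 3-month visit, some of them when acute toxicity can be expected. A transient AE at one of them could therefore cost the study a 3-month value that would have been obtainable.

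The loss is unlikely to be random. The Introduction says: "AEs developed due to RT, such as xerostomia, pain, mucositis, and decreased tongue volume, can induce swallowing dysfunction". It also expects RT to lower TP. If the patients who leave because of AEs or progression tend to have larger declines, the remaining patients will show too little decline and too few 'Impossible' results.

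**Working it through.** **Inputs**
- n = 40 (Section 2.7).
- SD of the change = 15.0 (Section 2.7). The sentence is garbled; 15.0 is read here as the SD.
- TP visits before the primary one: before RT, during RT, and 0 and 1 month after RT (Section 2.5.2 and the note to Table 1).
- Rate of unmeasurable TP: not given. The shares lost and the gaps below are assumptions.

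**1. The plan's own precision figure.** Section 2.7 gives a CI width of 4.0 ± 2.0. The half-width is 1.96 × 15/√40 = 4.65 with the normal quantile and 4.80 with t on 39 degrees of freedom; the full width is 9.30 or 9.59. None of these equals 4.0. The half-width lies within 2.0 to 6.0 only if 'width' means half-width and ± 2.0 is a tolerance. That is a separate matter; 4.8 serves here only as a yardstick.

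**2. One patient followed through the rules.** TP cannot be measured during RT because of an AE.
- Under Sections 2.5.1 and 2.8.2 the visit is 'Impossible', enters the during-RT ratio, and the patient is measured again at the next visit.
- Under Section 2.4 the patient meets a discontinuation criterion. If discontinued and not followed, the patient has no 3-month change and no 3-month 'Impossible' entry.
- The full analysis set does not repair this. The baseline value keeps the patient in the set, but there is no 3-month change to average.

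**3. Shift in the mean.** Let d be the share lost and g the amount by which their mean change is worse than that of the patients who remain. The mean of all patients is (1 − d) × (mean of remaining) + d × (mean of remaining − g), so the remaining patients' mean is too favourable by d × g.

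| Share lost | g = 5 | g = 10 | g = 15 |
|---|---|---|---|
| 5% | 0.25 | 0.5 | 0.75 |
| 10% | 0.5 | 1.0 | 1.5 |
| 20% | 1.0 | 2.0 | 3.0 |
| 30% | 1.5 | 3.0 | 4.5 |

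With 20% lost, 32 remain and the t half-width rises from 4.80 to 5.41 (SD still 15).

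**4. Extreme bound.** Suppose those lost are exactly the patients with the worst 3-month changes and changes are normal with SD 15. The shift is 15 × φ(z_d)/(1 − d):
- d = 10%: 15 × 0.195 = 2.92
- d = 20%: 15 × 0.350 = 5.25

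**5. The 'Impossible' ratio.** Suppose 8 of 40 (20%) are truly unmeasurable at 3 months. If 4 of them were discontinued earlier and leave the count, the ratio reads 4/36 = 11%. Only if all 8 had gone earlier would it read 0/32.

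**The case against.** Section 2.4 says difficult to measure, whereas Section 2.5.1 says impossible. A coherent plan could record single failures as 'Impossible' and end participation only when TP stays unmeasurable. The full protocol may say so, and a condensed article commonly leaves follow-up after discontinuation to it. The study is also single-arm and descriptive, with a sample size set by feasibility, so there is no hypothesis test to invalidate.

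Part of this stands. A reader might infer that one failed visit automatically removes a patient; Section 2.4 does not say that. Nor do the documents establish that the most severely affected patients leave. That is an inference from the Introduction, though a reasonable one.

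Three further readings go too far:
- Shifts of 2.9 and 5.2 units are not estimates of this rule's effect. They need assumed exit rates and the loss of exactly the worst changes, whereas a transient AE at an earlier visit need not mark the worst 3-month result.
- An 'Impossible' ratio near zero needs almost all failures to occur earlier and to leave the count. A patient first unmeasurable at 3 months can still be counted there.
- Selection could alter the correlation between TP and the Hyodo score, but no direction or size can be shown.

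The objection does not remove the conflict. The article states both rules, and gives neither a boundary between difficult and impossible nor an order of precedence. This is a contradiction between stated rules, not an omitted detail.

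**Conclusion.** The point holds as an unreconciled conflict between Section 2.4 and Sections 2.5.1, 2.8.1 and 2.8.2 that can cost primary-endpoint data. Followed as written, the discontinuation rule permits losses before 3 months that are probably outcome-related and would tend to understate both the decline in TP and the 'Impossible' ratio.

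The size is unknown. Under the assumed 5–30% lost and 5–15 units worse, the favourable shift runs from negligible to nearly the CI half-width of about 4.8. These figures cover all loss from the mean. The part caused by Section 2.4 is smaller, because a patient still unmeasurable at 3 months has no numeric change under either rule. The effect on the ratio depends on how many failures occur early and whether those patients leave the denominator, which the article does not fix.

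**What to change.** Reconcile Sections 2.4, 2.5.1, 2.8.1 and 2.8.2 as follows:
- Unmeasurable TP alone does not end study follow-up. Record 'Impossible' with its reason for that visit only, and re-attempt TP at the remaining scheduled visits.
- Leave VE and VF to the existing schedule, subject to the patient's condition and consent; Section 3 itself says that these examinations carry risk. Keep the other exit reasons in Section 2.4.
- At each visit, count patients unmeasurable because of AEs or progression in both the numerator and the denominator of the 'Impossible' ratio, and state that denominator.
- Report the mean change as applying to measurable patients, with the ratio beside it.

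This recovers patients who become measurable again and repairs the ratio. It does not by itself remove selection from the mean, which is why the last item is needed.

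The cost is a short amendment, since the visits are already scheduled. The downside is a few more attempted TP measurements in unwell patients. Section 2.1 describes the trial as ongoing, and values not collected after a discontinuation cannot be recovered at analysis, so the change is worth making early.

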### 2.5. Protocol of intervention

CRT or RT is the primary treatment for patients with OPC or HPC. However, concurrent chemotherapy regimens are not regulated. Adjuvant therapies, such as chemotherapy and secondary treatment using immune checkpoint inhibitors, are acceptable if needed.

#### 2.5.1. Method of TP measurement.

After the participants are fully informed, TP is measured 3 times at each evaluation point by a TP measurement device (JMS Tongue pressure measurement device. JMS Co., Ltd.), and the maximum TP values are recorded. After treatment, the change in TP value is analyzed. If TP measurement is impossible, it is recorded as “Impossible” accompanied by a description of the reason.

#### 2.5.2. Data collection.

Patient data will be collected before, during, and after RT, and at 0, 1, 3, and 6 months after the final date of RT (Table 1). TP measurement and VE will be conducted before, during, and after RT and 0, 1, 3, and 6 months after the final date of RT. VF will be conducted before and after RT and at 1, 3, and 6 months after the final date of RT.

**Table 1 F1:**
[figure not shown]
Overview of observation, clinical examination, and evaluation.

“Before RT (Baseline)” is defined as the date between the acquisition of written informed consent and the beginning of RT. “During RT” is defined as the date between 1 month ± 7 days after the first day of RT. “0 months after RT” is defined as the date from the final day of RT to 7 days after that. “1 month after RT” is defined as the date between 1 month ± 7 days after the final day of RT. “3 months after RT” is defined as the date between 3 months ± 14 days after the final day of RT. “6 months after RT” is defined as the date between 6 months ± 14 days after the final day of RT.

#### 2.5.3. Evaluation of VE.

The findings of the VE will be evaluated by the Hyodo score.^[25,26]^

The Hyodo score is defined as follows:

I.The salivary pooling degree at the vallecula and piriform sinuses.0:No pooling1:Pooling at the only vallecular.2:Pooling in the vallecula and piriform sinuses, but no penetration into the larynx.3:Pooling in the vallecula and piriform sinuses and penetration into the larynx.
II.The glottal closure reflex induced by touching the epiglottis or arytenoid.0:Marked reflex by 1 touch.1:Slow and/or weak reflex by 1 touch.2:Reflex by 2 or 3 touches.3:No reflex despite several touches.
III.The location of the bolus at the swallowing reflex initiation as assessed by “white-out” timing.0:Pharyngeal.1:Vallecula.2:Piriform sinuses.3:No swallowing reflex.
IV.The extent of pharyngeal clearance after blue-dyed water is swallowed.0:No residue.1:Pharyngeal residues remain but are absent after 2 or 3 swallows.2:Pharyngeal residues remain but there is no penetration into the larynx.3:Pharyngeal residues remain and there is penetration into the larynx.

#### 2.5.4. Evaluation of VF.

The evaluation of the VF has not yet been established. The VF findings will be described from the perspective below.

I.Oral stage.The contrast medium is kept in oral.Transition of the contrast medium from oral to pharyngeal.
II.Pharyngeal stage.Soft palate elevation and velopharyngeal function.The residual of the contrast medium at the vallecula and piriform sinuses.Aspiration and expectoration.Laryngeal elevation.Laryngeal closure.Pharyngoesophageal Segment Opening.Tongue Base Retraction.
III.Esophageal stage.Esophageal clearance and peristalsis.Counterflow in the esophagus.Diseases of and around the esophagus.

#### 2.5.5. Rehabilitation for dysphagia.

The participants will undergo RD to prevent or recover from functional decline in swallowing. RD was routinely scheduled as a protocol intervention during RT. The patients underwent the rehabilitation program in the morning and evening as follows:

Ice massage of the oral region (5 sets).Chin push-pull maneuver (10 seconds, 10 sets).Walking (3 minutes).

### 2.6. Endpoints

#### 2.6.1. Primary endpoint.

The primary endpoint was the change in maximum TP value from baseline to 3 months after RT.

#### 2.6.2. Secondary endpoint.

The secondary endpoints are listed as follows:

Changes in the maximum TP value from baseline to during RT as well as at 0, 1, and 6 months after RT. We performed the same analysis for the primary endpoint for each evaluation time.The findings of VE by the Hyodo score at each evaluation point.The findings of VF at each evaluation point.

### 2.7. Sample size consideration

The study aims to enroll 40 patients with OPC or HPC who will be treated with CRT or RT over 4 years. The target number of cases was set based on feasibility, given that approximately 12 patients are treated annually with these therapies at the institution. If the average ± SD expected to change in the primary endpoint maximum TP is estimated to be 15.0, the width of the 95% confidence interval (CI) will be appropriately 4.0 ± 2.0 based on a previous study.

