### 2.8. Statistical analysis

The “Full Analysis Set” is defined as the population that excludes study participants for whom no data on the maximum TP value are available. Analyses of the primary and secondary endpoints will be performed using the full analysis set.

All analyses will be performed after the data for all endpoints have been collected, reviewed, and fixed.

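### The stated 95% CI width of 4.0 ± 2.0 does not follow from the inputs printed with it (15.0 and 40 patients)

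*Protocol article*

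**What the plan says.** All the inputs stand in section 2.7 of the protocol article.

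- Size: "The study aims to enroll 40 patients with OPC or HPC who will be treated with CRT or RT over 4 years".
- Basis of that size: "The target number of cases was set based on feasibility, given that approximately 12 patients are treated annually with these therapies at the institution".
- Assumption for the primary endpoint: "If the average ± SD expected to change in the primary endpoint maximum TP is estimated to be 15.0".
- Precision claimed from it: "the width of the 95% confidence interval (CI) will be appropriately 4.0 ± 2.0 based on a previous study". I read the adverb as a slip for approximately.

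No unit is given for any of these figures, and the sentence does not identify the previous study.

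Section 2.8.1 fixes the analysis of the primary endpoint, to which the precision refers: "The average and 95% CI of the changes in the maximum TP value from baseline 3 months after RT will be analyzed as the primary". The article states no hypothesis test, margin or power. The full analysis set in section 2.8 is the "population that excludes study participants for whom no data on the maximum TP value are available".

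**The concern.** An average ± SD is a pair of numbers, and only one is printed. A CI width for a given n and SD is a single number, and a pair is printed. The reader must therefore guess which quantity 15.0 is, and whether 4.0, or 2.0, is a full or a half width.

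This matters because the trial is an estimation study. With the number of patients fixed by feasibility, the expected width of the interval is all the article offers to show what 40 patients can establish about the 3-month change. The rest of the article cannot fill the gap: it gives no other SD for the change, and the Introduction says that "the incidence and extent of the change have not yet been sufficiently clarified". A reader who takes 15.0 as the SD and ± 2.0 as the precision would expect a much tighter interval than that SD allows.

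**Working it through.** **Method.** For a one-sample mean change, the 95% CI half-width is t(0.975, n−1) × SD/√n, or 1.96 × SD/√n by the normal approximation. The full width is twice that. Inputs from section 2.7: n = 40, the figure 15.0, and the target 4.0 ± 2.0. √40 = 6.325 and t(0.975, 39) = 2.023.

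**Attempt to reproduce the plan's figure, taking 15.0 as the SD of the change.**

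- Standard error: 15/6.325 = 2.37.
- Half-width: 2.023 × 2.37 = 4.80 by t; 1.96 × 2.37 = 4.65 by z.
- Full width: 9.59 by t; 9.30 by z.
- Against 4.0 as a half-width: 4.65/4.0 = 1.16 and 4.80/4.0 = 1.20, so 16–20% too wide.
- Against 4.0 as a full width: 9.30/4.0 = 2.3 and 9.59/4.0 = 2.4.

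The figure is not reproduced either way. With SD 15.0, a half-width of 4.0 needs 55 patients (z) or 57 (t). A full width of 4.0, that is ± 2.0, needs 217 (z) or 219 (t).

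**Working back from the target at n = 40.**

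- Full width 4.0 (± 2.0): SD = 2.0 × 6.325/2.023 = 6.25 by t, or 2.0 × 6.325/1.96 = 6.45 by z.
- Half-width 4.0: SD = 12.5 by t, or 12.9 by z.

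None of these SDs appears in the article.

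**Other readings of the printed numbers, n = 40.**

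| Reading | Result |
|---|---|
| 15.0 is the mean change only | width not determined; 4.0 (± 2.0) needs an SD of 6.25–6.45, not given |
| 15.0 is the SD at each visit, so SD of change = 15√(2(1−ρ)) | full width 4.0 needs ρ of about 0.91; half-width 4.0 needs ρ of about 0.63–0.65; no correlation given |
| 15.0 is a variance (SD 3.87) | full width 2.4–2.5 |
| 15.0 is a total ± span (SD 7.5) | full width 4.65–4.80 |
| Numbers swapped, SD 2.0 | full width 1.2–1.3, not 15.0 |
| Numbers swapped, SD 4.0 | full width 2.5–2.6, not 15.0 |
| One-sided 95% limit with SD 15.0 | distance 3.90, but the plan states a 95% CI |

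**Could the ± 2.0 be the sampling variation of the width?** With SD 15.0 and n = 40, simulation gives the half-width a mean of 4.76 and a standard deviation of 0.54. The spread is not 2.0.

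**Effect of missing 3-month values (illustration only).** Section 2.4 allows for discontinuation and section 2.5.1 for readings that cannot be taken. If 20% had no 3-month value (my assumption), 32 patients remain. With SD 15.0 the half-width is then t(0.975, 31) × 15/√32 = 2.040 × 2.652 = 5.41, full width 10.8.

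**The case against.** The best defence is that a coherent reading exists. In the a ± b format the first number is the average, so 15.0 may be the expected mean change, with its SD lost in print. An SD of 6.5 would give 1.96 × 6.5/6.325 = 2.01, a full width of 4.0, and the pair could then mean a width of 4.0, that is ± 2.0. This stands as a possibility. A reader might infer that no reading can yield the stated width, and the documents do not support that. What remains is that the SD on which this reading depends is not in the article, so the figure cannot be checked.

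A second defence is that ± 4.65 to ± 4.80 lies within the range 2.0 to 6.0 that the pair literally spans. That is true, but the sentence does not present the pair as a range over uncertain SDs, and at one fixed n and SD the expected half-width is one value.

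Third, section 2.7 rests the 40 on feasibility: about 12 a year over 4 years is about 48, which is compatible with 40. A reader might conclude that the sample size has lost its only justification. It has not. The precision sentence is supplementary, and no analysis or decision rule depends on it.

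Fourth, the allowance for missing 3-month values may sit in the full protocol, and since the calculation cannot be reconstructed, the n it used is unknown. I accept this. Attrition is used here only as an illustration and is not a separate fault.

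**Conclusion.** The precision statement is wrong as written: it is not reproducible from its own inputs.

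The size of the discrepancy depends on the reading. If 15.0 is the SD of the change and all 40 patients are evaluable, the interval is mean ± 4.8 (± 4.65 by z), full width 9.6 (9.3). The factor of about 2.4 applies only if, in addition, 4.0 was meant as a full width. If it was meant as a half-width, the shortfall is 16–20%. If 15.0 is the mean, there may be no discrepancy at all, provided the unstated SD is about 6.3 to 6.5.

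The target of 40 stands on its feasibility basis. What fails is the only statistical support attached to it, and in an estimation trial that is the one design property a reader can use.

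**What to change.** Keep 40 on feasibility grounds and rewrite the precision sentence. Give the assumed mean change and its SD as two separate numbers, with the unit and the source study; say whether the full or the half width is meant; and recompute.

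- If 15.0 is the SD of the change, state that 40 evaluable patients give a 95% CI of mean ± 4.8 (full width 9.6). As an illustration under an assumed 20% without a 3-month value, add that 32 evaluable patients give ± 5.4 (full width 10.8).
- If a full width of 4.0 was intended, state the SD of about 6.3 on which it rests, and that all 40 are taken as evaluable.

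The cost is one sentence, with no extra patients and no change to the design or analysis. The drawback is that the stated precision may look less favourable.
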